### Safety evaluation and adverse events (AEs)

2.9

Participants will be continuously monitored for safety throughout each intervention session. All AEs occurring during the intervention or follow-up period will be recorded on case report forms (CRFs). In the event of an AE, qualified medical personnel will provide immediate symptomatic treatment, regardless of its suspected cause. The CRF will document the AE's onset, manifestations, severity, treatment, and outcome. Safety monitoring will continue until the participant's condition stabilizes or resolves.

A serious adverse event (SAE) is defined as any untoward medical occurrence that results in death, is life-threatening, requires hospitalization or prolongation of existing hospitalization, results in persistent or significant disability/incapacity, constitutes a congenital anomaly/birth defect, or requires medical intervention to prevent permanent impairment or damage. All AEs will be reported to the principal investigator (PI) and the institutional ethics committee for review, which will then determine whether the participant may continue the trial. Study-related SAEs will be compensated in accordance with regulatory and institutional requirements.

Based on clinical experience with these interventions, lumbopelvic manipulation is generally well tolerated, with potential treatment-related effects typically limited to transient muscle soreness or stiffness. To date, no study-related serious adverse events have been observed in our clinical practice. Baduanjin exercise, which consists of gentle, low-impact movements, is considered safe for postpartum women. Any adverse events that do occur will be recorded, managed, and reported according to the procedures described above.

### Data management and quality control

2.10

All clinical data collected by qualified physicians will be entered into a dedicated electronic database, with participant identities replaced by numerical codes. The principal investigator will be responsible for data quality at the study site. Quarterly investigator meetings will address trial-related issues and ensure procedural consistency. Telephone reminders for scheduled visits and assessments will be provided to participants to improve adherence. To monitor adherence to the protocol restriction on unrelated physiotherapy and medications, the following measures will be implemented: (1) participants will be instructed to maintain a daily log recording any additional treatments or medications used during the intervention period; (2) at each study visit (weeks 4, 8, and 12), participants will be systematically asked about their use of other therapies; and (3) weekly telephone calls will be made to reinforce the protocol requirements. Any deviation from the protocol will be recorded in the case report form and reported to the principal investigator. Participants who fail to comply with the protocol will be considered for withdrawal according to the predefined criteria.

### Sample size

2.11

The sample size was determined based on the primary outcome, the Numerical Pain Rating Scale (NPRS). The minimal clinically important difference (MCID) of the NPRS among patients with low back pain has been validated as 2 points on the 0–10 scale (21, 24). A between-group difference of 2 points in the change of NPRS from baseline was defined as a clinically meaningful threshold in the present study. We adopted a two-sided significance level of 0.05 and statistical power of 80%, and calculated sample size using the standard formula for the comparison of two independent means. Based on prior studies enrolling comparable low back pain populations (21, 24), the pooled standard deviation (SD) of NPRS change scores was estimated as 2.3. Given a minimal detectable between-group difference of 2 points, this calculation yielded a raw sample size of approximately 22 participants per group. Given the limited sample size of our preliminary pilot data (*n* = 12) leading to uncertain SD estimation, we further conducted a sensitivity analysis to test the robustness of our sample size calculation. When SD varied from 2.0 to 2.5, the unadjusted required sample size per group ranged from 16 to 26 participants prior to dropout adjustment. After accounting for an anticipated 20% participant dropout rate, the adjusted target sample size ranged from 20 to 33 participants per group. Our pre-specified recruitment target of 25 participants per group lies within this valid range, which guarantees adequate statistical power for the primary analysis focused on clinical pain outcomes (NPRS).

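### The SD range of 2.0 to 2.5 does not test the n = 12 uncertainty it cites, and a target of 25 per group inside the 20 to 33 range does not secure 80% power

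*Protocol article*

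**What the plan says.** Section 2.11 (Sample size) sizes the trial on the NPRS, with two-sided alpha 0.05, 80% power and a 2-point target: "A between-group difference of 2 points in the change of NPRS from baseline was defined as a clinically meaningful threshold". The SD has a stated origin: "Based on prior studies enrolling comparable low back pain populations (21, 24), the pooled standard deviation (SD) of NPRS change scores was estimated as 2.3". From these inputs the section reports about 22 per group before dropout.

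It then gives a reason for checking that figure: "Given the limited sample size of our preliminary pilot data (*n* = 12) leading to uncertain SD estimation, we further conducted a sensitivity analysis". The check is: "When SD varied from 2.0 to 2.5, the unadjusted required sample size per group ranged from 16 to 26 participants prior to dropout adjustment". Dropout is added next: "After accounting for an anticipated 20% participant dropout rate, the adjusted target sample size ranged from 20 to 33 participants per group". The section ends by saying that the recruitment target of 25 per group falls inside that range and that adequate power for the NPRS analysis is therefore assured.

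Section 2.12 (Statistical analysis) plans an intention-to-treat analysis with multiple imputation, and ANCOVA with the baseline value as covariate.

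**The concern.** Two steps in the reasoning do not connect.

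First, the uncertainty named is that of a pilot of 12, but the range examined is narrow, has no stated basis, and surrounds a value credited to the literature. It reaches 0.3 below 2.3 and only 0.2 above, and the upper side is the one that costs power.

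Second, a target lying inside a range of required sample sizes is adequate only for the SDs whose requirement it meets. The upper part of the range consists of requirements that 25 does not meet. If the assurance is accepted, readers will believe the trial has at least 80% power across the SDs examined. A null NPRS result would then be read as stronger evidence against a 2-point benefit than the design can provide.

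**Working it through.** **Inputs (Section 2.11).** Difference 2 points; two-sided alpha 0.05; power 80%; SD 2.3, varied from 2.0 to 2.5; dropout 20%; 25 recruited per group; pilot n = 12, with its SD not printed and no statement of whether 12 is the total or per arm.

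**Step 1: reproduce the plan's figures.** The normal formula is n per group = 2 × (1.96 + 0.8416)² × SD² / 2². The t-based value solves the power of the two-sample t-test (noncentral t). Requirements are rounded up, divided by 0.8 and rounded up again.

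| SD | Normal formula | t-based | Printed | Normal / 0.8 | t-based / 0.8 |
|---|---|---|---|---|---|
| 2.0 | 15.7 → 16 | 16.7 → 17 | 16 | 20 | 22 |
| 2.3 | 20.8 → 21 | 21.8 → 22 | about 22 | 27 | 28 |
| 2.5 | 24.5 → 25 | 25.5 → 26 | 26 | 32 | 33 |

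The printed adjusted range also reproduces: 16/0.8 = 20 and 26/0.8 = 32.5 → 33. Each printed figure comes from one formula or the other, but no single formula gives 16, 22 and 26 together.

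**Step 2: compare 25 with the plan's own adjusted requirement.** At SD 2.3 the need is 27 or 28 per group, and at SD 2.5 it is 32 or 33. The most lenient arithmetic, dividing the unrounded normal values by 0.8, gives 20.76/0.8 = 25.95 → 26 and 24.53/0.8 = 30.66 → 31. Every version exceeds 25.

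**Step 3: power at the fixed sample size.** Completers per group: 25 × 0.8 = 20. Two-sample t-test, noncentrality (2/SD) × √(n/2), with 38 df for n = 20 and 48 df for n = 25.

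| SD | 20 completing | 25 evaluable |
|---|---|---|
| 2.0 | 87% | 93% |
| 2.3 | 76% | 85% |
| 2.5 | 69% | 79% |
| 3.0 (assumed, outside the plan's range) | 54% | 64% |

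The normal approximation is slightly kinder with 20 completing: 78.5% at SD 2.3 and 71.6% at SD 2.5. With 20 completing, 80% power holds only up to an SD of about 2.20 (t) or 2.26 (normal), both below the plan's own 2.3. With 25 evaluable it holds up to about 2.47 (t) or 2.52 (normal).

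**Step 4: width of the SD range against n = 12.** The 95% limits for an SD are s × √(df/χ²) at the 97.5% and 2.5% points.

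- 11 df: 0.708s to 1.698s, ratio 2.40
- 10 df (12 in two groups): 0.699s to 1.755s, ratio 2.51
- 22 df (12 per arm): 0.773s to 1.415s, ratio 1.83

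The plan's range has ratio 2.5/2.0 = 1.25. These ratios do not depend on s, so the comparison does not need the pilot SD.

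**The case against.** The best defence is that the section names one source for 2.3, the prior studies, and mentions the pilot only to explain why a literature value was used and then varied. That is a fair reading. A reader might infer that the text claims two sources for the same SD and so contradicts itself. It does not go that far: no second SD is stated, and nothing says that 2.3 rests on the pilot. What stands is that the pilot's role is unexplained and the limits of 2.0 and 2.5 are unjustified.

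A reader might also put a confidence interval of about 1.6 to 3.9 around 2.3 and conclude that power could be below 40%. That needs the pilot SD to have been 2.3 and the 12 to be a total, and the document states neither. If 2.3 comes from the literature, a pilot interval is not its uncertainty. Only the comparison of ratios in Step 4 is free of that assumption.

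Section 2.12 keeps all randomised participants by multiple imputation, so it can be argued that 25 per group are analysed. Imputation does not restore the information lost with missing NPRS values, and Section 2.11 itself adjusts for dropout. Even with all 25 evaluable, t-test power at SD 2.5 is 79%, although the normal approximation gives 81%.

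Baseline-adjusted ANCOVA may recover some power, so the unadjusted figures may be conservative. This stands, but Section 2.11 claims no such gain and gives no correlation from which to compute it.

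**Conclusion.** The concern holds for the inference, not for the individual figures. The sensitivity range is much narrower than the uncertainty of a 12-person pilot, with a ratio of 1.25 against about 2.4 (1.8 if 12 per arm). The power assurance fails within the plan's own SD range: 76% at SD 2.3 and 69% at SD 2.5 with the 20 per group left after the planned dropout. The shortfall at the base-case SD is modest. If all 25 per group are evaluable, power there is 85%.

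These figures assume an unadjusted two-sample t-test on change scores, equal SDs, a true 2-point difference and the stated 20% dropout. The figure at SD 3.0 is an illustration, because the documents give no basis for a specific upper SD.

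The mix of formulas is real but minor, at one participant per group. A reader might infer that 16 is wrong and must be 17; it is equally consistent to keep 16 and change 22 and 26 to 21 and 25. Nor does the point show that the trial must be enlarged. It shows that the stated power property is not one the design has.

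**What to change.** Rewrite the paragraph in Section 2.11:

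1. State which source gives 2.3 and what role the pilot has. If the pilot is kept as a reason for uncertainty, print its SD and say whether 12 is the total or per arm.
2. Use one formula throughout: 16, 21 and 25, or 17, 22 and 26, for SD 2.0, 2.3 and 2.5, with the dropout-adjusted figures to match.
3. Remove the assurance of adequate power. Print the power at 25 recruited and 20 completing per group across an SD range with a stated basis that extends above 2.5. Label any SD beyond the sourced values as an assumption, for example 54% at SD 3.0 with 20 completing.
4. Note that the baseline-adjusted ANCOVA in Section 2.12 may recover some power, but that no correlation is stated and no gain is counted.

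The cost is one reworded paragraph and a less favourable power statement. No extra patients, visits or procedures are needed.

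### The claim that 25 per group guarantees adequate power does not follow from the plan's own figures: its base case with 20% dropout needs 28 per group

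*Protocol article*

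**What the plan says.** All of the relevant text on size is in section 2.11 (Sample size) of the protocol article.

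- Effect: "A between-group difference of 2 points in the change of NPRS from baseline was defined as a clinically meaningful threshold".
- Variability: "the pooled standard deviation (SD) of NPRS change scores was estimated as 2.3", attributed to earlier studies in low back pain.
- Error rates and method: two-sided 5%, 80% power, and the usual formula for two independent means.
- Base-case result: "this calculation yielded a raw sample size of approximately 22 participants per group".
- Sensitivity analysis: "When SD varied from 2.0 to 2.5, the unadjusted required sample size per group ranged from 16 to 26 participants prior to dropout adjustment".
- Dropout: "After accounting for an anticipated 20% participant dropout rate, the adjusted target sample size ranged from 20 to 33 participants per group".
- Conclusion: "Our pre-specified recruitment target of 25 participants per group lies within this valid range, which guarantees adequate statistical power for the primary analysis".

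The abstract and sections 2.1 and 2.3 confirm 50 participants in total. Section 2.12 (Statistical analysis) plans an ANCOVA with the baseline value as covariate, in an intention-to-treat analysis with multiple imputation.

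**The concern.** The dropout allowance is applied to the two ends of the SD range but not to the case on which the trial was sized. The reader is never shown the dropout-adjusted requirement at SD 2.3, and that requirement exceeds the target.

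The argument offered in its place is that 25 lies between 20 and 33. Those two numbers are requirements under different SDs. A target between them meets the requirement for the smaller SDs and misses it for the larger ones, so being inside the range cannot guarantee power.

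This is the power statement for the primary outcome. If the trial finds no difference in pain, readers will rely on it to judge whether a 2-point effect was likely to have been missed.

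**Working it through.** **Inputs (section 2.11):** difference 2; SD 2.3, range 2.0 to 2.5; two-sided alpha 0.05; power 80%; dropout 20%; 25 enrolled per group.

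**Step 1. Reproduce the plan's figures.** With the normal approximation, n per group = 2 × (1.960 + 0.842)² × SD² / 2². The t-based n comes from the noncentral t distribution.

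| SD | Normal, unrounded | Normal n | t-based n | Plan |
|---|---|---|---|---|
| 2.0 | 15.7 | 16 | 17 | 16 |
| 2.3 | 20.8 | 21 | 22 | about 22 |
| 2.5 | 24.5 | 25 | 26 | 26 |

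The plan's figures reproduce to within one participant.

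**Step 2. Identify the dropout convention.** Dividing by 1 − 0.20 gives 16/0.8 = 20 and 26/0.8 = 32.5, so 33. This matches the printed 20 to 33. Multiplying by 1.2 would give 26 × 1.2 = 31.2, so 32, which does not match.

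**Step 3. Apply it to the base case.** 22/0.8 = 27.5, so 28 per group (56 in total). Starting from the normal-approximation 21 gives 21/0.8 = 26.25, so 27. Even the multiplying convention gives 21 × 1.2 = 25.2 (26) or 22 × 1.2 = 26.4 (27). No variant gives 25. Put the other way, keeping 22 of 25 allows a dropout of only 3/25 = 12%.

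**Step 4. Power at the planned size.** 25 × 0.8 = 20 per group. The noncentrality is 2 / (SD × √(2/n)).

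| SD | 20 per group, t | 20 per group, normal | 25 per group (no dropout), t | 25 per group (no dropout), normal |
|---|---|---|---|---|
| 2.0 | 86.9% | 88.5% | 93.4% | 94.2% |
| 2.3 | 76.4% | 78.5% | 85.4% | 86.7% |
| 2.5 | 69.3% | 71.6% | 79.1% | 80.7% |

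With 20 per group, 80% is reached only if the SD is at most about 2.20 (t) or 2.26 (normal). Both are below the base-case 2.3.

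**Step 5. Power of the planned ANCOVA.** Assume equal variances at baseline and follow-up, with correlation r between them. Adjusting for baseline then changes the effective SD from the change-score SD to SD × √((1 + r)/2). The documents give no value for r, so a range is shown for 20 per group (t based).

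| r (assumed) | Effective SD from 2.3 | Power |
|---|---|---|
| 0.3 | 1.85 | 91% |
| 0.5 | 1.99 | 87% |
| 0.7 | 2.12 | 83% |
| 0.8 | 2.18 | 81% |
| 0.9 | 2.24 | 78% |

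Setting the effective SD equal to the 2.20 cut-off gives the correlation at which power drops to 80%. At SD 2.3 it is 2 × (2.20/2.3)² − 1 = 0.83. At SD 2.5 it is 2 × (2.20/2.5)² − 1 = 0.55, or 2 × (2.257/2.5)² − 1 = 0.63 with the unrounded normal cut-off, so about 0.6.

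**The case against.** The strongest defence is that the two-means formula is not the analysis the trial will run. Section 2.12 plans a baseline-adjusted ANCOVA, which at SD 2.3 keeps power above 80% with 20 per group for any correlation up to about 0.8. This stands as a reason not to call the trial underpowered. It does not rescue the text: section 2.11 states no correlation, takes no credit for the adjustment, and its own upper SD of 2.5 falls below 80% from a correlation of about 0.6.

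A second defence is that 20 evaluable per group is pessimistic. Some women counted as dropouts under section 2.4.4, for example for low adherence, stay in the intention-to-treat set and may still report pain, and imputation can draw on their other visits. That is partial mitigation. Imputation does not in general restore the information lost with a missing outcome, and the plan itself inflates for dropout.

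Third, the base-case gap is small: 3.6 points by the t test and 1.5 by the normal approximation, with the requirement itself described only as approximate. That is fair. The larger shortfall, 8 to 11 points, arises at SD 2.5.

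A reader might also infer that the SD has two conflicting sources, because the sensitivity analysis is introduced with "Given the limited sample size of our preliminary pilot data". The text does not establish that. It attributes 2.3 to earlier studies and mentions the pilot of 12 only as the reason for varying the SD.

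**Conclusion.** The point holds as a fault in the stated justification. On the plan's own inputs and its own dropout convention, the base case needs 28 per group against 25 planned. Under the formula it names, the planned size gives about 76% to 79% power at SD 2.3 after 20% dropout, and 69% to 72% to 87% to 89% across SD 2.5 to 2.0. The guarantee is wrong because it depends on the SD being at most about 2.20 to 2.26.

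A reader might go further and conclude that the trial will not have 80% power or must enrol more women. The documents do not support that. With the planned ANCOVA, power at SD 2.3 is about 87% at a correlation of 0.5, 81% at 0.8 and 78% at 0.9. Those figures rest on an assumed correlation and equal variances at the two time points, so they show what is possible and do not replace a calculation in the plan. The design, the endpoint and the type I error are unaffected.

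**What to change.** In section 2.11, delete the statement that 25 per group guarantees adequate power, together with the argument that it lies within the range. Then do one of the following.

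1. Keep the two-means calculation and state that 25 per group with 20% dropout leaves 20, giving about 76% power at SD 2.3, 69% at SD 2.5 and 87% at SD 2.0 (t test).
2. Justify 25 per group through the ANCOVA in section 2.12, stating the assumed baseline-to-follow-up correlation and its source, with power shown over a range of correlations and SDs.

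The cost is a few sentences and, under the first option, a less favourable power figure. No extra patients are needed, and nothing in the conduct of the trial changes.

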### Statistical analysis

2.12

All statistical analyses will be performed using SPSS version 26.0. Primary analyses will be conducted on an intention-to-treat (ITT) basis, including all randomized participants in their originally assigned groups regardless of protocol adherence or withdrawal. Missing data will be handled via multiple imputation (MI), the gold-standard approach for missing continuous clinical outcome data in randomized controlled trials. Last observation carried forward (LOCF) will not be adopted in the present study, as this single-imputation method is prone to bias and has been widely discouraged in contemporary statistical guidelines. Continuous variables will first be tested for normality using the Shapiro-Wilk test. Normally distributed data will be reported as mean ± standard deviation (SD), whereas non-normally distributed data will be presented as median (first quartile, third quartile) [M (P25, P75)]. For within-group comparisons, paired-sample t-tests will be applied to normally distributed data, and Wilcoxon signed-rank tests to non-normally distributed data. For between-group comparisons at baseline, independent-sample t-tests will be used for normally distributed data, and Mann-Whitney U tests for non-normally distributed data. To compare post-intervention outcomes between the two groups, analysis of covariance (ANCOVA) will be performed, with baseline values as covariates to adjust for potential baseline imbalance. In addition, potential confounding variables—including postpartum duration (months since delivery), age, and baseline outcome values—will be recorded and considered as covariates in the primary analyses where appropriate. Exploratory correlation analyses will employ Pearson or Spearman correlation coefficients, as appropriate, to examine associations among post-intervention pain intensity (NPRS), the Oswestry Disability Index (ODI), the SF-36, core muscle activation (%MVIC), and mean power frequency (MPF). These analyses are hypothesis-generating and will be interpreted with caution; formal corrections for multiple comparisons will not be implemented. All tests will be two-sided, and a *P*-value < 0.05 will indicate statistical significance. Given the exploratory nature of these analyses and the multiple comparisons involved, the results should be interpreted as hypothesis-generating, and any statistically significant findings will require confirmation in future studies.

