**Figure 1 F1:**
[figure not shown]
Trial flow diagram.

**Table 1 T1:** Trial schedule.

Study period	Enrolment	Intervention	Follow-up	
Time point	Baseline (Week 0)	Week 4	Week 8	Week 12
Eligibility screen	√			
Informed consent	√			
Randomization/allocation	√			
Intervention manipulation		1–4 weeks		
NPRS	√	√	√	√
ODI	√	√	√	√
SF-36	√	√	√	√
sEMG	√	√		
Adverse events monitoring	Any time during the intervention and follow-up			

√, required; NPRS, Numerical Rating Scale; ODI, Oswestry Disability Index; SF-36, 36-Item Short Form Health Survey; sEMG, Surface electromyography.

The primary objective of this study is to evaluate the efficacy of lumbopelvic manipulation combined with Baduanjin exercise for reducing pain and improving functional outcomes in patients with postpartum low back pain. The secondary objective is to explore the neuromuscular mechanisms underlying this combined intervention using surface electromyography.

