## Discussion

3

This study protocol presents a randomized controlled trial evaluating the efficacy and neuromuscular mechanisms of lumbopelvic manipulation combined with Baduanjin exercise for postpartum low back pain. The ‘prepare-then-train' sequence is grounded in clinical experience and theoretical reasoning, although direct comparative evidence is currently limited (15). This study is designed to provide objective sEMG evidence to test this hypothesis.

Given the limited data on postpartum populations and the scarcity of objective neuromuscular assessments in this field (9), our protocol addresses these gaps by combining validated patient-reported outcomes (NPRS, ODI, SF-36) with quantitative sEMG parameters (%MVIC and MPF). This design allows us to assess whether improvements in pain and function are accompanied by objective changes in core muscle activation and fatigue resistance.

Assessing muscle fatigue and endurance is particularly relevant in the postpartum population (26). Pregnancy and childbirth lead to reduced endurance of the core musculature which compromises spinal and pelvic stability (27). Compounding this physiological decline, postpartum women face substantial physical demands, including frequent bending, lifting, and carrying of the infant, as well as breastfeeding, all of which impose repetitive loads on the lumbopelvic region and may accelerate muscle fatigue (28). Therefore, evaluating changes in MPF—a sensitive frequency-domain indicator of muscle fatigue—provides insight into whether the combined intervention improves the ability of the lumbar extensor muscles to resist fatigue during functional tasks, which may be a key mechanism underlying its therapeutic effects.

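### The planned correlations of week-4 levels do not show whether pain improvement goes with muscle change; they should be adjusted for baseline and arm

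*Protocol article*

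**What the plan says.** Protocol article, section 2.12 (Statistical analysis), names the method, "Exploratory correlation analyses will employ Pearson or Spearman correlation coefficients, as appropriate", and the variables and time point: "to examine associations among post-intervention pain intensity (NPRS), the Oswestry Disability Index (ODI), the SF-36, core muscle activation (%MVIC", with MPF completing the list. On one grammatical reading the post-intervention qualifier covers NPRS only, but no reading of the sentence yields change scores.

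Baseline adjustment appears in the same section for the between-group comparison: "analysis of covariance (ANCOVA) will be performed, with baseline values as covariates to adjust for potential baseline imbalance". Postpartum duration, age and baseline values are further possible covariates, but for the primary analyses. Nothing extends either statement to the correlations, and the section does not say whether the arms are pooled.

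The status of the correlations is plain: "These analyses are hypothesis-generating and will be interpreted with caution; formal corrections for multiple comparisons will not be implemented".

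Section 3 (Discussion) says the design will show "whether improvements in pain and function are accompanied by objective changes in core muscle activation and fatigue resistance". The secondary objective, given after Table 1 in section 2.1, is to "explore the neuromuscular mechanisms underlying this combined intervention using surface electromyography". Table 1 and section 2.8.4 show that NPRS, ODI, SF-36 and sEMG are all measured at weeks 0 and 4.

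**The concern.** The Discussion's question is about change, while the planned coefficient describes levels at one visit. A week-4 correlation combines up to three components:

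- the arm difference on both variables, if the arms are pooled;
- the lasting relation between a woman's usual pain and her usual muscle activity, carried forward from baseline;
- the link between her pain response and her muscle response.

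The third is the one that answers whether improvement goes with muscle change within women. A significant coefficient could therefore arise without it. If the components have opposite signs, a real link could be masked. Since no other stated analysis connects pain with sEMG within women, a reader of the results would have nothing to set against a misleading coefficient.

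**Working it through.** **The plan's own figure.** The article gives no figure for the correlations. Section 2.11 supplies the sample size and the planned effect: a 2-point difference, SD 2.3, two-sided alpha 0.05, power 80%. The normal formula gives 2 × [2.3 × (1.960 + 0.842)/2]² = 20.8, so 21 per group. The t-based version gives 21.8, so 22, which agrees with the stated 22. The planned total is 50.

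**Inputs.**
- From the document: n = 50, 1:1, and d1 = 2/2.3 = 0.87 for NPRS. The 2.3 is the SD of change, used here in place of the week-4 SD, which is not given.
- Assumed, because the document gives none: sEMG shift d2 of 0.5 to 1.0 SD; baseline correlation r0 up to 0.5 in either direction; stability s (baseline to week 4) of 0.5 to 0.7.
- Signs are set so that the arm effect gives a positive r.

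**Null condition.** Week-4 value = s × baseline + arm shift + independent residual, with total within-arm variance 1. Given arm and both baselines, pain and sEMG are unrelated at week 4.

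**Arm shifts alone, arms pooled.** r = d1·d2 / √[(d1² + 4)(d2² + 4)].
- d2 = 0.5: 0.435/√(4.756 × 4.25) = 0.435/4.496 = 0.097; P < 0.05 in about 10% of trials.
- d2 = 1.0: 0.870/√(4.756 × 5) = 0.870/4.876 = 0.178; about 24%.

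**Adding a baseline correlation, d2 = 0.5.** r = (s²·r0 + d1·d2/4) / √[(1 + d1²/4)(1 + d2²/4)] = (s²·r0 + 0.109)/1.124. Rejection rates come from simulation at n = 50.

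| r0 | s | s²·r0 | pooled r | P < 0.05 |
|---|---|---|---|---|
| 0.2 | 0.5 | 0.050 | 0.14 | 17% |
| 0.3 | 0.7 | 0.147 | 0.23 | 37% |
| 0.5 | 0.7 | 0.245 | 0.31 | 63% |
| −0.2 | 0.5 | −0.050 | 0.05 | 6% |
| −0.3 | 0.7 | −0.147 | −0.03 | 5.5% |
| −0.5 | 0.7 | −0.245 | −0.12 | 12.5% |

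The partial correlation adjusting for arm and both baselines rejects in about 5% under this null. With 40 complete cases (20% dropout), 37% becomes about 30% and 63% about 51%.

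**No arm effect.** With r0 = 0.3 and s = 0.7, the level correlation is still significant in about 17% to 18% of trials. Splitting or adjusting by arm alone would not remove this part.

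**A different model.** Each woman has a stable trait carrying 0.6 of the variance, and her changes are independent.
- Trait correlation of −0.3 or −0.5 with no arm effect: mean r −0.17 or −0.30, significant in 23% or 58%.
- Pooled change scores, no trait correlation, d1 = 0.87 and d2 = 0.5 to 1.0: still significant in 12% to 32%. Change scores alone are therefore not enough if the arms are pooled.
- Arm-adjusted change scores: about 5%.
- Partial correlation: about 5% to 9% across the settings run (including trait share 0.8), because one noisy baseline does not capture the trait fully.

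**The case against.** The strongest reply is that the Discussion's sentence describes the design as a whole and can be read at group level: does sEMG improve in the arm in which pain improves? The baseline-adjusted ANCOVA and the paired tests address that reading, and section 2.8.4 separately plans a before-and-after comparison of MPF. This stands. A reader might infer that the correlations are the only support for the mechanism objective. The documents do not support that, since the between-arm ANCOVA of sEMG serves the same objective, rests on randomisation and is unaffected.

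Second, section 2.12 calls the analysis hypothesis-generating and asks for confirmation. Section 3 repeats the caution and discloses that the correlations were not prespecified in the registration. This limits the consequence. It does not alter what is estimated, and a later study using the same coefficient would reproduce the same mixture.

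Third, a reader might infer that the arms will be pooled. The text does not say so, and a condensed article may leave this to the analysis plan. The arm component is therefore conditional, and alone it is modest. The between-woman component does not depend on pooling.

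Fourth, a reader might take 63% as the false-positive rate. It is the top of an assumed range with same-direction baseline correlations only; opposite signs give about 6% to 13%. Nor is the simulated null one of unrelated changes: under it, changes within an arm correlate at (1 − s)·r0/2, which is 0.3 × 0.3/2 = 0.045 at r0 = 0.3, s = 0.7, and 0.5 × 0.5/2 = 0.125 at r0 = 0.5, s = 0.5. The rates refer to no association given arm and baselines.

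**Conclusion.** The point holds in limited form. Section 2.12 fixes simple correlations of week-4 levels, and these cannot answer a within-woman question about improvement and muscle change. Under the assumptions listed, a nominal 5% test rejects in about 10% to 24% of trials from arm shifts alone. It rejects in about 17% to 63% when a same-direction baseline correlation is added to a 0.5 SD sEMG shift, and in about 6% to 13% when the baseline correlation runs the other way and the components partly cancel. The sEMG shift, baseline correlation and stability are all assumed, so these figures show sensitivity and do not predict this trial's error rate. Severity is minor to moderate, since neither the primary conclusion nor the randomised sEMG comparison depends on this analysis.

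**What to change.** Replace the correlation sentence in section 2.12 with text to this effect:

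> Associations of week-4 NPRS, ODI and SF-36 with week-4 %MVIC and MPF will be estimated as partial correlations (rank-based where needed), adjusting for arm and for the baseline values of both variables. Each will be reported with a 95% CI and shown descriptively by arm. These analyses are hypothesis-generating, and an association measured at the same visit does not by itself establish a mechanism.

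If change scores are preferred, or added as a check against a noisy baseline, they too need adjustment for arm.

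The cost is wording and three degrees of freedom per coefficient (48 to 45 at n = 50). Every variable is already collected at weeks 0 and 4, so no extra visit, measurement or participant is needed.
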